# Three donor site dressings in pediatric split-thickness skin grafts: study protocol for a randomised controlled trial

**DOI:** 10.1186/s13063-015-0557-9

**Published:** 2015-02-08

**Keywords:** Pediatric, Burns, Split-thickness skin graft, Donor site, Dressing, Randomised controlled trial, Pain, Scar, Itch, Re-epithelialisation

## Abstract

**Background:**

For children requiring split-thickness skin grafting for burn injury, the optimum donor site dressing is an ongoing subject of debate. The most common dressings in use, both regionally and worldwide, are calcium alginates. We will compare an alginate with two other dressings, all of which are in current use in the Pegg Leditschke Paediatric Burns Centre (PLPBC), to determine which dressing performs the best.

**Methods/Design:**

This is a randomised, prospective single center parallel three-arm trial comparing three donor site wound (DSW) dressings: Algisite™ M, a calcium alginate dressing; Cuticerin™, a smooth acetate gauze impregnated with water-repellent ointment (petrolatum, paraffin and Eucerite®) and Sorbact®, a gauze mesh coated with a dialkylcarbamoyl chloride (DACC) and amorphous hydrogel.

Primary outcomes are days to complete DSW healing, and pain. Previously validated measures will be used for all outcomes. Secondary outcomes are: itch; scar appearance at three, six and 12 months; ease of dressing application and removal and dressing costs and utility. Results will be analysed on an intention-to-treat basis. Donor site thickness will be measured with a small biopsy from the center of the graft, to document the depth of the DSW across the groups.

**Discussion:**

This study will provide comprehensive short- and long-term data on DSW dressings in pediatric split-thickness skin grafting. The best-performing dressing will become the preferred dressing for the PLPBC. We will provide rigorous data against which other dressings can be compared in future, recognising that alginates are the most common DSW dressing currently in use. Our study design replicates a real-world scenario in order to identify clinically significant differences between the three dressings.

**Trial registration:**

This trial was prospectively registered on 8 April 2014 with the Australia and New Zealand Clinical Trials Register (identifier: ACTRN12614000380695).

**Electronic supplementary material:**

The online version of this article (doi:10.1186/s13063-015-0557-9) contains supplementary material, which is available to authorized users.

## Background

Split-thickness skin grafting (STSG) is the most widely used method of achieving skin coverage in burns that are not predicted to heal rapidly with dressings. In harvesting skin to cover the defect, a second wound is created, the donor site wound (DSW). In children, this wound is predicted to re-epithelialise in seven to 14 days. The ideal DSW dressing does not adhere to the wound bed, facilitating removal. DSW dressings should be pain-free, reduce blood loss and be changed infrequently; ideally not until the wound has healed [1-4]. Among clinicians, a pain-free dressing is the most consistently desirable or essential quality of a wound dressing, in recognition of the fact that the DSW is often more painful than the recipient site [5]. The need for such a dressing is, if anything, more important in pediatric burn care as there are data suggesting that decreased pain leads to measurable and clinically significant improvements in wound healing [6-8]. Additionally, rapid healing permits the repeat harvesting of donor areas in larger burns and also decreases the risk of scarring [9].

The optimum dressing for the DSW is unclear, with surgeon and centre choice appearing to follow tradition stemming from eminence as often as it follows selection stemming from evidence. Alginates are the most commonly used DSW dressing [2,3]. There are four systematic reviews investigating DSW dressings [10-13], none of which have identified a single dressing with a clearly superior performance. Data are particularly lacking in pediatric burns, and new dressings are being developed continually. There is a clear need for high quality evidence in pediatric DSW dressings.

Due to the sparse data available, and in recognition of the variety of dressings in our unit, we aim to investigate DSW dressings currently in use in the PLPBC. This trial seeks to answer the following question: in pediatric STSGs, which of the three DSW dressings currently in use at our institution (Algisite™ M, Cuticerin™ and Sorbact®) is superior in terms of pain and itch, wound healing, ease of application and removal, scarring and costs? The best-performing dressing will become our preferred standard, against which we are likely to subsequently repeat the trial as newer dressings become available.

### The Pegg Leditschke Paediatric Burns Centre

The Pegg Leditschke Paediatric Burns Centre (PLPBC) is the major pediatric burns centre for Queensland and Northern New South Wales in Australia, serving a population of approximately 4.5 million. The PLPBC treats approximately 750 new burns annually. A total of 79 patients received split-thickness skin grafts in 2013. The majority of patients have small areas requiring grafting, and our preferred donor site is the thigh or buttock. On occasion grafts from the adjacent skin are used to combine donor and graft sites into a single dressing site. Facial burns are preferentially treated with scalp grafts whereas larger burns may require using the back as a donor site.

The PLPBC promotes ‘bench to bedside, and back to bench’ burns care. Clinical questions drive our research efforts, the result of which alter clinical care and in turn generate the next round of research questions. The centre has research and prevention arms, as well a clinical multidisciplinary team. The PLPBC has numerous publications in pediatric burns across many different aspects of this care; laboratory, clinical burns care, patient and family response to burn injury, prevention, rehabilitation, physio- and occupational therapy and procedural pain control and distraction modalities.

## Methods/Design

### Protocol and registration

This trial has approval from the Royal Children’s Hospital Human Research Ethics Committee (approval number: HREC/14/QRCH/36), and from the University of Queensland Medical Research Ethics Committee (approval number: 2014000447)*.* The methodology is specified in advance, documented in a protocol and has been registered prior to recruitment commencing (Australia and New Zealand Clinical Trials Register, identifier: ACTRN12614000380695) [14]. The methods are summarised here according to the revised Consolidated Standards for Reporting Trials (CONSORT) statement [15].

### Design and setting

We have designed a single centre prospective parallel randomised controlled trial with three treatment groups (Figure 1). There is no control arm in the generally accepted sense, but we recognise many will view alginates as a *de facto* control arm. Equipoise exists for this trial as there is no generally accepted DSW dressing among burns surgeons in general, and among the PLPBC surgeons in particular. We deem it unethical to have an inactive control arm as our purpose is to find which of three current dressings is superior.

**Figure 1 Fig1:**
[figure not shown]
**Flow diagram of the trial.** DSW, donor site wound; PLPBC, Pegg Leditschke Paediatric Burns Centre.

The PLPBC will be moving to a new children’s hospital in the same city in the middle of this trial (expected date is late November 2014). All clinical staff will remain the same, and we have systems in place to manage this transition with no disruption to acute services. While this migration will be accompanied by a moratorium on elective surgery, this will not be the case for children enrolled in the trial and requiring acute surgery. Their operations and follow-up procedures and/or assessments will not be delayed or postponed due to the migration.

### Eligibility criteria for patients

From recruitment commencement, all patients of the PLPBC requiring STSG will be consecutively considered for inclusion, until recruitment is completed. Our unit treats only pediatric patients, aged from birth to 15 years. Regardless of the predicted size of the DSW, all children undergoing STSG will be considered for inclusion.

Patients will be assessed for eligibility by their primary surgeon or an investigator. If eligible, they will be approached by a trained staff member not involved in their primary care. Parent or caregiver informed consent will be obtained and documented. Where appropriate, child assent will be documented (Additional files 1 and 2).

Exclusion criteria include non-English speaking parents or caregivers, as we will not be able to gather data the following day by telephone. Also excluded are children with a known cognitive impairment, and children under the care or investigation of the Department of Communities, Child Safety and Disability Services. Only thigh or buttock DSWs will be included.

### Interventions

There is uniformity in the application of all three dressings within the PLPBC; all are dressings that are already in use. Three different DSW dressings will be used: Algisite™ M, an alginate dressing (Smith & Nephew, Hull, United Kingdom); Cuticerin™, a smooth acetate gauze impregnated with water repellent ointment (petrolatum, paraffin and Eucerite®) (Smith & Nephew, Hull, United Kingdom) and Sorbact®, a gauze mesh coated with a dialkylcarbamoyl chloride (DACC) and amorphous hydrogel (Abigo Medical AB, Gothenburg, Sweden). DACC is a synthetic fatty acid derivative. This dressing is designed to cause a hydrophobic interaction between bacteria and the dressing, lifting them from the wound bed in a moist environment [16].

We no longer routinely use open weave paraffin gauze or similar dressings directly on DSWs. The large mesh spaces in these dressings can lead to incorporation during re-epithelialisation which in turn can cause pain and bleeding on dressing removal. Further, leaving such a dressing on until spontaneous separation risks a permanent pattern on the DSW scar [17].

### Surgical procedure

The grafting procedure will be performed with a pneumatic dermatome (Zimmer Inc., Warsaw, Indiana, United States), according to local practice. The STSG will be harvested at between 0.005 and 0.008 of an inch (0.13 to 0.20 mm), according to surgeon preference and the age of the patient. It is anticipated that the majority will be taken with the dermatome set at 0.007 of an inch (0.18 mm), as this is the default local setting. The particular dermatome used will be recorded, as will the ‘swipe number’ of the dermatome blade in use at the time, the donor site and the surgeon harvesting the graft. A small lentiform biopsy will be taken from the center of each graft, blocked, cut and measured for graft thickness. Any remaining donor skin at the conclusion of the case will be similarly treated. This will allow more confidence regarding DSW depth when analysing results.

Following harvesting, local anesthetic (bupivacaine 0.25% with epinephrine 1:200,000 AstraZeneca Pty Ltd, North Ryde, NSW 2113, Australia) is applied directly onto the wound up to the maximum safe dose calculated from the weight of the child (2 to 2.5 mg/kg, depending on the child and any co-morbidities). Post-harvest topical application of local anesthetic was chosen rather than pre-harvest infiltration in order to further standardise the DSW, as infiltration was felt to be more variable. Topical local anesthetic gives good pain relief in DSWs [18]. In longer cases donor sites may be temporarily dressed with epinephrine and/or saline-soaked gauze (1 mg/1,000 mL NaCl), with or without pressure dressings, to facilitate hemostasis. The DSW is formally dressed at the end of the case, following dressing of the grafted site. One of the three dressings is applied directly to the wound; followed by an absorbent second layer of Allevyn™ and a Hypafix™ securement dressing (Smith & Nephew, Hull, United Kingdom). The majority of patients are sent home the same day.

### Wound treatment

Randomisation occurs immediately before the definitive DSW dressing is applied. Where space between donor sites permits (for example, between the left thigh and right thigh), a second randomisation is permitted. Each wound then constitutes its own study entity and will be analysed separately.

The DSW dressing is taken down in clinic on the seventh post-operative day. Our current standard dressing following this first dressing change is Xeroform® (Covidien, Mansfield Massachusetts, United States) 3% bismuth tribromophenate occlusive petrolatum gauze, which will be applied to all DSWs from this point. We expect the majority of wounds to be healed or nearly healed at seven days, from clinical observation. We have no experience using any of the three study dressings on a DSW beyond this first dressing change.

Clinics occur every weekday, and each patient is seen twice weekly after the first dressing change. This is predicated on ongoing treatment for the grafted site. By reviewing the donor dressing on these occasions we will avoid a requirement for additional clinic visits. Reviewing the dressings every three days after the first week replicates a real-world scenario and means that our results, if positive, will have clinical significance for this outcome.

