### Study outcomes

#### Primary endpoints

There are two primary endpoints: pain, and time to re-epithelialisation. Pain will be assessed at several time points. Firstly, at four hours following completion of the operation. This will allow measurement in day-case patients prior to their discharge. By taking these scores face to face we hope to facilitate the telephone call the following day. It is also an opportunity to clarify directly with parents that we are scoring DSW pain, rather than graft site pain. Secondly, at one day later via a telephone call, or following ward review for inpatients. Thirdly, immediately before premedication prior to removal of the DSW dressing in clinic. Premedication will be with oxycodone 0.1 mg/kg orally (Mundipharma Pty Ltd, Sydney, NSW 2000, Australia), and oral paracetamol 150 mg/kg (sanofi-aventis Australia Pty Ltd, Macquarie Park, NSW 2113, Australia). Fourthly, at two minutes following removal of the DSW dressing. The graft dressing will not be taken down until after these scores are recorded. If a dressing is reapplied, the recordings at time points two, three and four above will be repeated for each subsequent change.

A variety of scales will be used for assessing pain, determined by who is performing the assessment (observer, parent or child), and by the age of the child. The face, legs, activity, cry and consolability (FLACC) scale will be used by nursing staff [20]. Where children are old enough, the Revised Faces Pain Scale (FPS-R) will be used for patient self-reporting of pain [21]. We will collect FPS-R data for children aged from three years, recognising that data are sparse for children below the age of five years [21]. Parents will use an 11-point (0 to 10) numeric rating scale (NRS). This, rather than a visual analogue scale, was chosen to facilitate the accuracy of recording during a telephone call.

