### Randomisation

Randomisation will occur in the operating theatre, immediately prior to application of the DSW dressing. We have used unrestricted randomisation, generated using an online program (http://stattrek.com/) [26]. Randomisation of participants will continue until each of the study groups has a minimum of 28 participants reaching the primary endpoints. Allocation concealment will be via the use of sequentially numbered, sealed opaque envelopes pre-prepared by a third party.

Patients will be recruited into the trial when a decision to graft is made following review of the burn injury. The patient will be randomised intra-operatively, further separating recruitment and consent from randomisation.

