### Sample size

The sample size calculation was derived from the primary outcomes. Dressings are changed every three days after the first week, and we have used three days as a minimum clinically important difference (MCID) for re-epithelialisation. The standard deviation (SD) on DSW healing, from our database, is four days. We have chosen to power the study to 80%, with an α of 0.05, requiring 28 participants in each group. This sample size is also adequate to determine an MCID of 2 (SD 2.5) in our pain scores using the FLACC and the NRS.

We will use simple randomisation in order to maintain the same degree of DSW dressing unpredictability for each subject. Recruitment will continue until there are at least 28 participants in each arm with primary outcome data. A two-year recruitment period is anticipated, based upon the number of eligible patients requiring grafting in our unit in previous years.

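### A child may be randomised twice with each wound analysed as its own entity, but pain and itch scores in such a child cannot be cleanly credited to one dressing, and the target counts participants

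*Protocol article*

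**What the plan says.** Under Wound treatment, the protocol article allows two allocations in one child: "Where space between donor sites permits (for example, between the left thigh and right thigh), a second randomisation is permitted". It then sets the unit of analysis: "Each wound then constitutes its own study entity and will be analysed separately".

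Under Primary endpoints, pain is one of two: "There are two primary endpoints: pain, and time to re-epithelialisation". The observer measure is specified as follows: "The face, legs, activity, cry and consolability (FLACC) scale will be used by nursing staff". Children from three years give an FPS-R score and parents a 0 to 10 NRS. Pain is scored four hours after surgery, a day later, before premedication in clinic, and two minutes after the dressing is removed. Itch is scored on the Itch Man Scale at the same times (Secondary endpoints). The only instruction on location is that "we are scoring DSW pain, rather than graft site pain".

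The target is expressed in participants. Randomisation says "Randomisation of participants will continue until each of the study groups has a minimum of 28 participants reaching the primary endpoints", and Sample size says "Recruitment will continue until there are at least 28 participants in each arm with primary outcome data". Data analysis specifies generalised linear models with variance suited to repeated measures where needed, and makes intention to treat primary. It does not mention two wounds in one child.

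**The concern.** Allocation is unrestricted. If the three arms are equally likely, two wounds on one child receive different dressings two times in three. At the first three pain assessments both dressings are in place, so a whole-child score reflects both. The article separates donor site from graft site but not one donor site from another. Making each wound an entity then requires a pain value for each wound, without saying how one is obtained.

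The first consequence is for the pain and itch comparisons. A score that mixes two dressings pulls the arms together, in a trial meant to choose the unit's preferred dressing.

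The second is the unit of counting. The rule under Wound treatment works in wounds, the stopping rule works in participants, and the sample size treats the units as independent. Healing and scar can be measured on each wound, so for them the question is only whether the correlation between two wounds on one child is modelled.

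**Working it through.** **Inputs from the article (Sample size; Data analysis).** Healing: difference 3 days, SD 4. Pain: difference 2, SD 2.5. Alpha 0.05 two-sided, power 80%, 28 per group.

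**Reproducing the planned size.** n per group = 2(1.96 + 0.84)² SD² / difference².
- Healing: 2 × 7.85 × 16 / 9 = 27.9, so 28, with power 0.801 by the normal approximation (0.787 by the t-test).
- Pain: 2 × 7.85 × 6.25 / 4 = 24.5, so 25. At 28 per group, power is 0.849 (normal) or 0.836 (t-test).

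The stated 28 reproduces as a pairwise comparison of independent subjects.

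**Dilution of pain in two-wound children.** Three assumptions are mine: the child's score reflects the average effect of the two dressings, the second wound goes to A, B or C with probability 1/3 each, and the same score is entered for both wounds.
- In a record labelled A, the weight on A's mean is 1/2 + (1/2)(1/3) = 2/3.
- In a record labelled B, the weight on A's mean is (1/2)(1/3) = 1/6.
- The A minus B contrast is therefore multiplied by 2/3 - 1/6 = 1/2.

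With a share f of wounds from two-wound children, the overall factor is (1 - f) + 0.5f = 1 - 0.5f. The article does not give f, so a range is shown. Power is from the two-sample t-test, SD 2.5, 28 records per arm.

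| Assumed f | Apparent difference | Power |
|---|---|---|
| 0% | 2.0 | 0.836 |
| 5% | 1.95 | 0.818 |
| 10% | 1.9 | 0.798 |
| 20% | 1.8 | 0.754 |
| 30% | 1.7 | 0.705 |

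A simulation that keeps the shared scores agrees. With 9 two-wound children among 84 wounds (f = 18/84 = 21%), the mean difference was 1.79 and power 0.75. Type I error stayed near 0.05. The harm to pain is thus dilution rather than false positives.

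**Healing.** Each wound has its own value, so there is no dilution. Ignoring the correlation matters in a direction that depends on how pairs fall. As an illustration, take 28 wounds per arm and an assumed within-child correlation of 0.5 or 0.8. With four same-arm pairs in each arm, a nominal 5% test rejects 6.8% or 7.7% of the time. With four pairs split between the two arms, it rejects 4.3% or 3.7%.

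**One record per child.** Let g be the share of children with two wounds. Then f = 2g/(1 + g), so g = f/(2 - f). With the child assigned to the first randomised wound, the factor is 1 - 0.5g. At f = 20%, g = 0.2/1.8 = 11%, the apparent difference is 2 × (1 - 0.056) = 1.89, and power with 28 children per arm is 0.79.

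**Dropping two-wound children instead.** At f = 20% and 28 wounds per arm, 28 × 0.8 = 22.4 wounds per arm remain. Power is 0.74, no better than the 0.75 with dilution.

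**The case against.** The strongest reply is that nothing in the article says one score is entered under two dressings. A reader might infer that from the unit-of-analysis rule, but it remains an inference. Parent NRS and child FPS-R could be asked for each wound, and the score after removal could be separated if the dressings came off at different times. The case record forms that might show this are not part of the article. This stands: the double entry is conditional, and only FLACC is whole-child by construction. It does not rescue FLACC at the first three time points, when both dressings are on.

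Second, the repeated-measures wording under Data analysis can be read to cover two wounds in one child, and analysing wounds separately need not mean assuming independence. For healing and scar that is a fair reading, and one sentence would settle it. It does not help pain, because a variance correction cannot decide which dressing a shared score belongs to.

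Third, a reader might conclude that the trial will have fewer than 28 children per arm. The documents do not support that. Both places that set the target say participants, so counting wounds is only a possibility opened by the conflicting unit.

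Fourth, two-wound children may be rare. The article says most patients need small grafted areas, and Trial status reports 34 patients randomised to one of the three dressings without mentioning a second allocation. At f = 10% or less, power for pain stays at about 80% or above.

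**Conclusion.** The point holds in a limited form. The article fixes a unit of analysis that does not fit pain and itch, and it conflicts with a target and sample size expressed in independent participants. In a two-wound child, a FLACC score, and any other score not asked per wound, cannot be cleanly credited to one dressing.

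The size depends on f, which is not given. If one averaged score is entered for both wounds, a 2-point difference appears as 1.9, 1.8 or 1.7 and power falls from 84% to 80%, 75% or 71% at an assumed 10%, 20% or 30% of wounds. If scores are collected per wound, the loss for parent and child ratings is smaller. For healing, scar and removal the matter is within-child correlation only, with no fixed direction.

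**What to change.** Replace the instruction to analyse wounds separately with three statements.

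1. Wound-level outcomes (healing, scar, removal) keep every wound, with child as a random effect or GEE cluster.
2. Pain and itch are analysed with one record per child. All children stay in under intention to treat, assigned to the dressing of the first randomised wound, or the child's score is modelled on both dressings received. A sensitivity analysis leaves out two-wound children, with that status defined by donor sites before the first envelope is opened. Without that condition the exclusion could depend on the first allocation, because the second randomisation is permitted rather than required.
3. The target of 28 per arm counts children, by first randomised wound.

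Leaving two-wound children out of the primary pain comparison is not advised: it conflicts with intention to treat and, as shown above, need not recover power.

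The cost is slightly more analysis work and, if wounds were being counted, possibly a few more children to reach 28 per arm. Some dilution remains in two-wound children under the first-wound rule. The third statement clarifies a stopping rule in a trial already recruiting, so it should be recorded as a dated clarification before analysis.
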